## Methods/Design

### Design

This study is a multi-center open-labeled randomized controlled trial with two groups: MBCT+ TAU vs. TAU. The study has been approved by the Medical Ethics Committee Arnhem-Nijmegen (nr. 2012/339) for all participating sites. Before randomization, written informed consent is obtained from all participants. Primary and secondary outcome measures are assessed at baseline and after MBCT + TAU (8–12 weeks) or after a TAU-period (8–12 weeks). Participants allocated to the TAU condition are offered participation in the MBCT after completion of the TAU-period and first follow-up assessment. Of all participants who completed the MBCT, follow-up measures take place at three and six months after the end of treatment. For an overview of the recruitment and measurement points see Fig. 1.

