### Follow-up assessments

The first follow-up measure takes place after the MBCT training or the TAU-period. The MINI depression module is administered face-to-face or by phone and participants fill out the questionnaires either online or on paper. Participants are asked about changes in pharmacological or psychological treatment during the study period. Also participants deciding to discontinue MBCT are asked to participate in follow-up measures. In all MBCT completers (MBCT + TAU and participants of the TAU group who followed the MBCT after the TAU-period), the same follow-up measures are administered at three and six months after end of treatment. Due to logistic reasons it is not possible to keep assessors blind. To assess the inter-rater reliability of the MINI, all diagnostic interviews are audio taped and a randomly selected sample will be reassessed by an independent rater. For an overview of all measurement assessments see Table 1.

**Table 1 Tab1:** Overview of measures and corresponding measurement time points

Measure	Target concept	Baseline	FU1	FU2	FU3	FU4
IDS-SR	Depressive symptoms	●	●	●	●	●
MINI-depr. module	Diagnosis of major depression	●	●	●	●	●
WHOQOL-BREF	Quality of life	●	●	●	●	●
RRS-EXT	Rumination	●	●	●	●	●
FFMQ	Mindfulness skills	●	●	●	●	●
SCS	Self-compassion	●	●	●	●	●
MINI interview	Comorbid psychiatric disorders	●				
DM-TRD	Treatment-resistance	●				
CTQ	Childhood trauma	●				

*FU1:* 2 weeks post intervention (MBCT + TAU)/8-12 weeks post baseline (TAU), *FU2:* 3 months post intervention (MBCT+ TAU)/2 weeks post intervention (TAU), *FU3:* 6 months post intervention (MBCT + TAU)/3 months post intervention(TAU), *FU4:* 6 months post intervention (TAU)

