### Analyses plan

The MBCT + TAU and TAU conditions will be compared on baseline sample characteristics to ensure that all possible meaningful characteristics were evenly distributed across the conditions. To examine treatment outcome, we will use both intention-to-treat and per-protocol samples. Participants are considered completers of the MBCT if they attend at least four sessions of MBCT. To examine whether effects for participants experiencing a depressive episode for one to two years and participants meeting criteria for chronic depression according to the DSM-IV (≥2 years) are different, the primary and secondary analyses will be repeated in these subgroups.

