### Primary analysis

The effect of condition (MBCT + TAU vs. TAU) on the primary outcome measure (depressive symptoms) will be examined using general linear models. Condition and baseline score of depressive symptoms will be included as independent variables, depressive symptoms at FU1 as the dependent variable. Because MBCT is delivered in mixed groups consisting of regular patients and a few study participants and previous studies did not yield an effect of therapy group [20], we will not incorporate a random group effect.

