### Secondary analyses

Effects on quality of life, rumination, mindfulness skills, and self-compassion will also be investigated using general linear models with the same independent variable as in the primary analysis. To investigate effects on remission rates a χ^2^ test will be performed. Moderating effects of level of treatment-resistance and childhood trauma will be investigated by including an interaction effect (condition*moderator) in the models. Furthermore, exploratory analyses on rumination, mindfulness skills and self-compassion as possible underlying mechanisms of change will be conducted. Consolidation and moderation of treatment effect will be investigated in the whole sample of MBCT completers (MBCT + TAU and TAU) using end-of-treatment assessments and follow-up assessments at three and six months after end of treatment.

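### At three and six months only MBCT completers, pooled over both arms, are studied, so moderation of treatment effect cannot be identified there and consolidation is an uncontrolled, selected change

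*Protocol article*

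**What the plan says.** All references are to the protocol article.

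- **Sample (Secondary analyses):** "Consolidation and moderation of treatment effect will be investigated in the whole sample of MBCT completers (MBCT + TAU and TAU".
- **Time points (same sentence):** "using end-of-treatment assessments and follow-up assessments at three and six months after end of treatment". In Table 1 these are FU1, FU2 and FU3 for the MBCT + TAU arm, and FU2, FU3 and FU4 for TAU patients who take MBCT later.
- **Completer (Analyses plan):** "Participants are considered completers of the MBCT if they attend at least four sessions of MBCT".
- **Who is measured late (Design):** "Of all participants who completed the MBCT, follow-up measures take place at three and six months after the end of treatment". The Abstract and the Follow-up assessments section give the same restriction.
- **Control arm after FU1 (Design):** "Participants allocated to the TAU condition are offered participation in the MBCT after completion of the TAU-period and first follow-up assessment". No TAU comparison is described beyond that point.
- **Moderation in the randomised comparison (Secondary analyses):** "Moderating effects of level of treatment-resistance and childhood trauma will be investigated by including an interaction effect (condition*moderator) in the models".
- **Primary analysis:** "Condition and baseline score of depressive symptoms will be included as independent variables, depressive symptoms at FU1 as the dependent variable".

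**The concern.** Moderation of a treatment effect means that the difference between treated and untreated patients varies with a baseline characteristic. Estimating it needs both treated and untreated patients, and the sample named for three and six months has only treated ones. A characteristic that predicts a poor course under any care would appear there as a moderator. The two moderators the plan names, treatment resistance and childhood trauma, are both plausibly prognostic.

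Consolidation has a related weakness. It is a change within persons, in a sample defined by attendance after randomisation and, for the TAU arm, also by the choice to take MBCT. Patients may change medication or add treatment freely during the study (Participants, TAU), so natural course and co-treatment are mixed into the change.

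These are the trial's only data on durability in a chronically ill population. Under the completer rule, early leavers have no three- or six-month data. A statistical analysis plan written later cannot recover measurements that were never taken.

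**Working it through.** **The plan's own figure.** No sample size or precision is given for the completer analysis. The only stated figure is for the primary ANCOVA, and it reproduces. With d = 0.53, correlation 0.5, two-sided alpha 0.05 and power 80%, the normal approximation is 2 × (1.96 + 0.84)² × (1 − 0.5²) / 0.53² = 41.9, so 42 per arm. The exact noncentral-t calculation gives 43 (power 0.801). Then 2 × 43 + 8 = 94. Nothing below changes this.

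**Step 1: can moderation be formed?** In the randomised models the moderation term is condition × moderator. In the pooled completer sample every patient has received MBCT, so there is no treated-versus-untreated contrast. Original allocation still varies, but there it separates immediate from delayed MBCT, not MBCT from no MBCT. Only an association between moderator and outcome or course remains.

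**Step 2: how readily would prognosis pass for moderation?** Assumptions, none from the documents: true moderation zero, prognostic correlation r = 0.3 with outcome level, 60 to 80 completers. The approximate chance of a significant result is Φ(atanh(r) × √(n − 3) − 1.96), with atanh(0.3) = 0.3095.

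- n = 60: 0.3095 × √57 − 1.96 = 0.377, giving 65%.
- n = 80: 0.3095 × √77 − 1.96 = 0.756, giving 78%.

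A simulation compared this with the randomised interaction test (3,000 runs per row, SD about 1, baseline correlation 0.5, baseline score in both models, no true moderation):

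| Prognostic slope (SD) | Randomised interaction, 86 patients | Moderator–outcome test, 70 pooled completers |
|---|---|---|
| 0 | 4% | 5% |
| 0.2 | 5% | 47% |
| 0.3 | 5% | 79% |
| 0.4 | 5% | 95% |

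The randomised test stays near 5%. The completer test detects prognosis, as it should, but the plan would call the result moderation.

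**Step 3: what does completer selection do to level and change?** The completers' mean differs from the mean of all treated patients by (share of non-completers) × (gap between non-completers and completers). With an assumed share of 15% to 35% and an assumed gap of 0.3 to 0.5 SD, this is 0.15 × 0.3 = 0.045 SD to 0.35 × 0.5 = 0.175 SD in the favourable direction.

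That concerns level, not change. A second simulation set the true mean change after end of treatment to zero and varied what drives completion (76% to 79% completed; positive means worse symptoms):

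| Completion depends on | Completers' change to six months (SD) | Completers' six-month level minus all treated (SD) |
|---|---|---|
| End-of-treatment score | +0.10 | −0.10 |
| Stable trait | 0.00 | −0.10 |
| Later slope | −0.03 | −0.03 |

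The level looked better among completers in all three cases. The bias in change was unfavourable, absent or favourable, depending on the mechanism.

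**The case against.** The strongest reply is that the plan already tests moderation properly, with a condition-by-moderator term in the models comparing randomised conditions, and that the primary FU1 comparison has nothing to do with completers. Both points stand. They limit the problem to one secondary analysis, but they do not give that analysis a control group.

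Four stronger readings are tempting, and the documents do not support them.

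- **Maintenance is overstated.** The analysis starts from end of treatment in the same patients. As the second table shows, selection can bias the change either way.
- **The plan contradicts itself on discontinuers.** The Follow-up assessments section says: "Also participants deciding to discontinue MBCT are asked to participate in follow-up measures". That sentence follows the description of the first follow-up and precedes the separate completer rule for three and six months. Read in order it concerns FU1, and there is no conflict.
- **The two arms are pooled with no term for allocation.** Pooling is stated. The absence of a term is only silence in a condensed article and may be settled elsewhere.
- **Only patients who stayed to the end are followed.** Four of eight sessions suffice, so patients who leave halfway are included. Early leavers are the ones lost.

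It is also fair to say that 65% to 78% is simply the power of an unadjusted correlation test under assumed inputs. It illustrates the mislabelling and is not this trial's error rate.

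**Conclusion.** The point holds within limits. In the pooled completers, moderation of treatment effect is not identifiable at three and six months; only predictors of course after MBCT are. That follows from the stated design and needs no numerical assumption. Consolidation there is an uncontrolled within-person change, open to selection bias whose direction the documents do not fix. Completers' absolute level probably looks better than that of all treated patients. The 0.045 to 0.175 SD range for this rests on an assumed non-completer share and gap, and the 65% to 78% figure on an assumed r = 0.3 and n = 60 to 80.

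A reader might infer that the trial cannot study moderation at all. It can, in the randomised comparison at FU1. The point should be acted on, but it does not threaten the trial's main result.

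**What to change.** 1. Reserve the term moderation for the condition-by-moderator interaction in the randomised FU1 comparison. Rename the pooled analysis *predictors of course after MBCT* and state that it is uncontrolled.
2. Offer the three- and six-month assessments to all patients allocated to MBCT + TAU and to all TAU patients who start MBCT, regardless of sessions attended.
3. Analyse all of them with time and original allocation (immediate versus delayed MBCT) in the model. Show the randomised MBCT arm separately and keep the completer analysis as supplementary.

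The renaming costs nothing. The added follow-up needs a small amendment and uses the existing online or paper questionnaires and telephone MINI for a limited number of patients. Some non-completers will decline, so selection is reduced rather than removed. The moderation claim becomes narrower, and the later follow-up still has no concurrent TAU group.

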## Discussion

Despite the range of currently available treatments options such as antidepressant medication and cognitive behavioral or interpersonal therapy, a substantial number of currently depressed patients do not recover [10]. Chronic, treatment-resistant depression is associated with a high personal as well as societal burden [4, 5]. Additional treatment options are required, to further reduce depressive symptoms and to improve quality of life in this population.

In previous pilot studies, MBCT appeared to be a promising treatment option for patients with chronic depression. Besides incorporating effective elements of cognitive behavioral therapy, MBCT focuses on acknowledging negative emotions and thoughts and disengaging from maladaptive automatic cognitive and behavioral patterns elicited by them. As chronic, treatment-resistant depression is characterized by perseverance of symptoms and a long treatment history, maladaptive automatic thinking patterns are likely to have become habitual. Therefore MBCT might be a very valuable additional treatment for this group. In the current study we will build upon the previous pilot findings by studying the effect of MBCT on depressive symptoms in a large chronic, treatment-resistant sample in a randomized controlled trial.

Strauss and colleagues [19] argue that MBCT might be as effective as cognitive behavioral therapy in reducing depressive symptoms in currently depressed patients. The results of the current study will provide an indication of the effectiveness of MBCT over and above available pharmacological and psychological treatments such as CBT and IPT, in patients who previously received these types of psychological treatment.

In addition to the effects of MBCT on depressive symptoms, we will investigate if MBCT leads to less rumination and higher quality of life in this patient population. Moreover, this trial will inform clinicians and researchers if chronic, treatment-resistant depressed patients are able to learn mindfulness skills and to develop more self-compassion by following a standard MBCT training. This large trial will also give more detailed information about the acceptability and effect sizes of MBCT in this target group.

The ecological validity of the study will be high, as participants will be enrolled in standard Dutch MBCT courses offered at mental health care institutions. If the conclusion will be that MBCT is effective in reducing depressive symptoms in chronic, treatment-resistant depression, this study could make a significant impact on treatment options for this severely depressed target group.

## Abbreviations

ADM: Antidepressant medication
CBT: Cognitive behavioral therapy
CTQ-SF: Childhood Trauma Questionnaire-short form
DM-TRD: Dutch measure of treatment resistant depression
DSM-IV: Diagnostic and statistical manual of mental disorders- 4^th^ edition
FFMQ: Five facet mindfulness questionnaire
IDS-SR: Inventory of Depressive Symptomatology- Self Report
IPT: Interpersonal therapy
MBCT: Mindfulness-based Cognitive Therapy
MINI: Mini International Neuropsychiatric Interview
RRS-EXT: Ruminative response scale extended version
SCS: Self compassion scale
TAU: Treatment as usual
WHOQoL-BREF: World health organization quality of life scale
